### Clinical therapists’ views of the intervention

A workshop will be held with clinical therapists from a range of local stroke services to provide feedback on the ARC and control treatments delivered during the RCT. One therapist from each of the study sites will also be invited to shadow the delivery of the ARC intervention during the study to allow for feedback to inform a future multi-centre trial.

### Study withdrawal

No specific study withdrawal criteria have been set. Participants may withdraw from the study at any time for any reason. Should a patient decide to withdraw from the study, a reason for withdrawal will be sought but patients can chose to withdraw without providing an explanation. If a participant decides to withdraw, it will not affect the normal care they receive. Data collected prior to withdrawal will be used in the study analysis unless consent for this is specifically withdrawn.

If a participant does not wish to continue to complete the treatments, they will be asked if they are willing to continue to attend outcome assessments.

Clinical teams, local treatment providers or investigators may also withdraw participants from the study at any time if they feel it is no longer in the participant’s interest to continue, for example, because of intercurrent illness.

### Safety

The safety of the intervention will be evaluated by examining the occurrence of adverse events and falls.

### Falls

Falls diaries will be given to each participant to complete. The providers (a research physiotherapist and a research associate) will check these weekly during face-to-face visits, and any falls between the 6 and 10-week outcome measures will be confirmed by the outcome assessor. Throughout the trial, the following definition of a fall will be applied: ‘A fall is described as an event in which the participant has lost their balance and landed on the floor or ground or lower level, including a slip or trip’ [44]. The falls diaries will be collected by the study team on the final outcome assessment visit.

### Safety evaluation

The standard definitions for adverse events will be used in this study:

#### Adverse event

Any untoward medical occurrence in a subject to whom a study intervention or procedure has been administered, including occurrences which are not necessarily caused by or related to that intervention. An adverse event (AE), therefore, does not necessarily have a causal relationship with the treatment. In this context, ‘treatment’ includes all interventions (including comparative agents) administered during the course of the study. Medical conditions/diseases present before starting study treatment are only considered adverse events if they worsen after starting study treatment.

#### Related AE

Related AE is an AE that results from administration of any of the research study procedures. All AEs judged by either the reporting investigator or the sponsor as having reasonable causal relationship to a study procedure qualify as ‘related adverse events’. The expression “reasonable causal relationship” means to convey in general that there is evidence or argument to suggest a causal relationship.

#### Causality

The assignment of the causality should be made by the investigator responsible for the care of the participant. All adverse events judged as having a reasonable suspected causal relationship to a study procedure are considered to be related adverse events. If any doubt about the causality exists, the local investigator (PI) should inform the chief investigator. In the case of discrepant views on causality between the investigator and others, all parties will discuss the case. In the event that no agreement is made, the main REC and other bodies will be informed of both points of view.

#### Serious adverse event

Serious adverse event (SAE) is an untoward occurrence that:
Results in deathIs life-threatening (refers to an event in which the subject was at risk of death at the time of the event; it does not refer to an event which hypothetically might have caused death if it were more severe)Requires hospitalisation, or prolongation of existing hospitalisationResults in persistent or significant disability or incapacityConsists of a congenital anomaly or birth defectIs otherwise considered medically significant by the investigator

Medical judgement should be exercised in deciding whether an AE is serious in other situations. Important medical events that are not immediately life-threatening or do not result in death or hospitalisation but may jeopardise the patient or may require intervention to prevent one of the other outcomes listed in the definition above, should also be considered serious.

#### Unexpected adverse event

Unexpected adverse event is an adverse event that is not an expected occurrence in the circumstances of this trial.

#### Recording and reporting of adverse events

This study will only report adverse events which are considered to be serious.

Serious adverse events *exclude*:
Pre-planned hospitalisationsScheduled treatment for pre-existing conditions.

The capture of potential SAEs will take place at the study outcome assessments by including the following questions in the outcome proforma: “are there any new medical problems since the last study assessment?” In addition, we will specifically enquire about falls in response to the participants falls diaries. For any events which fulfil the criteria to be a SAE and are unreported, the study SAE form will be completed.

Events considered to be SAEs will subsequently be documented onto a separate study SAE form, and a causality and expectedness assessment will be performed. As study investigators or other members of the research team may become aware of SAEs at times other than at outcome assessment appointments, the SAE form will also be used to directly capture these events.

Initial/provisional SAE reports can be made by telephone or email to the study co-ordinating centre. All initial/provisional reports must be followed by a fully completed SAE form. If incomplete information is available at the time of this initial report, further information must be provided on a follow-up form as soon as it is available. All SAEs regardless of causality or expectedness will be reported to the chief investigator and trial sponsor (Northumbria NHS Foundation Trust) in line with local policies. The main REC will be notified of related and unexpected SAEs within 15 days of the chief investigator becoming aware of the event.

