**Methods:**

This pilot observer blind randomised controlled feasibility trial aims to recruit 60 participants over 15 months from community stroke services in the North East of England. Participants will be within 24 months of stroke onset causing new problems with mobility. Each participant will be randomised to the study intervention or control group. Intervention treatment participants will undertake 18 auditory rhythmical cueing (ARC) treatment sessions over 6 weeks (3 × 30 min per week, 6 supervised (physiotherapist/research associate)/12 self-managed) in a home/community setting. A metronome will be used to provide ARC during a series of balance and gait exercises, which will be gradually progressed. The control treatment participants will undertake the same duration balance and gait exercise training programme as the intervention group but without the ARC. Feasibility will be determined in terms of recruitment, retention, adverse events, adherence, collection of descriptive clinical and accelerometer motor performance data at baseline, 6 weeks and 10 weeks and description of participant, provider and clinical therapists’ experiences. As well as using questionnaires to collate participant views, qualitative interviews will be undertaken to further understand how the intervention is delivered in practice in a community setting and to identify aspects perceived important by participants.

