### Study objectives

Primary objectives:
To identify monthly recruitment rates to determine whether it is possible to enrol at least one patient per month from each study centre.To report participant adherence to ARC intervention and control treatment arms (provider observation and exercise diaries).To assess the acceptability and completeness of proposed methods of data collection to ensure they are feasible for a definitive trial.

Secondary objectives:
4.To report participant retention to the study.5.To report the success of outcome assessor blinding to participant treatment allocation.6.To report adverse events in control and intervention treatments during the study.7.To report the views of study participants about undertaking the ARC intervention at home and in the community.8.To report the views of providers and clinical therapists about the study protocol.9.To gather data to allow reporting of summary statistics to allow estimation of the sample size requirements for the definitive trial.

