### Data analysis

Objectives 1–3: Recruitment will be described as rate/month (total and per site). Adherence will be described using data from the exercise diaries (number of planned sessions completed). Acceptability and completeness of methods of data collection will be described using percentages from both treatments.

Objective 4: Retention will be described as percentage from both treatments.

Objective 5: The success of outcome measurement blinding will be described (%).

Objective 6: Adverse events pertaining to the study for each treatment will be described (number of events).

Objective 7: The views of study participants about undertaking the ARC treatment at home and in the community will be described. Summary statistics will be used for answers to closed questions and open questions will be thematically analysed.

Objective 8: The views of providers and clinical therapists about delivery of the study treatments will be described. Summary statistics will be used for answers to closed questions and open questions will be thematically analysed.

Objective 9: As this is a pilot study, statistical comparisons of clinical outcomes (e.g. dynamic gait index, see above) and accelerometer data between treatments will not be undertaken and data will be presented as summary descriptive statistics. To determine which outcome measures to take forwards to a main trial, we plan to review data completeness, patient/staff feedback about acceptability and any new emerging literature about most appropriate measures, to inform decisions. This review will also determine the most appropriate primary outcome measure. Data collected for this selected primary outcome measure (e.g. standard deviation) will subsequently be used as appropriate by statisticians to inform a power calculation for a definitive trial.

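### The serious-only reporting rule contradicts objective 6 and the safety section, and leaves non-serious treatment-related events other than falls without a count by arm

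*Protocol article*

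**What the plan says.** Four places in the protocol article commit to adverse events with no limit on seriousness:

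- Abstract, Methods: "Feasibility will be determined in terms of recruitment, retention, adverse events, adherence", among other items.
- Study objectives, secondary objective 6: "To report adverse events in control and intervention treatments during the study".
- Safety: "The safety of the intervention will be evaluated by examining the occurrence of adverse events and falls".
- Data analysis, objective 6: "Adverse events pertaining to the study for each treatment will be described (number of events").

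The definitions are equally broad. An adverse event is "Any untoward medical occurrence in a subject to whom a study intervention or procedure has been administered", whether or not it is caused by the treatment. The next definition reads "Related AE is an AE that results from administration of any of the research study procedures", again without regard to seriousness.

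Recording and reporting of adverse events then narrows this: "This study will only report adverse events which are considered to be serious". The same section continues: "The capture of potential SAEs will take place at the study outcome assessments by including the following questions in the outcome proforma". The question asks about new medical problems since the last assessment. The only form named is the SAE form, and a causality and expectedness assessment is described for the events entered on it.

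Falls have their own route. The Falls section gives every participant a diary, defines a fall without requiring injury, has providers check the diaries weekly, and has the outcome assessor confirm falls between 6 and 10 weeks.

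**The concern.** Objective 6 and its analysis need a count of study-related adverse events in each arm. The recording section supplies that count for serious events only. A non-serious event that a participant attributes to the exercises may be mentioned in answer to the outcome-visit question, but the article gives no form on which to enter it, no step at which its relation to treatment is judged, and no table in which it appears.

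This matters because tolerability is part of what the pilot is meant to pass on to a multi-centre trial. Participants are stroke survivors with gait impairment, and 12 of the 18 sessions are done independently. If the pilot reports few or no adverse events, a reader who has seen objective 6 will take that as evidence about all adverse events, when part of the explanation would be the reporting rule.

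**Working it through.** **Step 1. Compare the sections.**

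| Place in the article | Scope of events | By arm? |
|---|---|---|
| Abstract, Methods | adverse events, no limit | not stated |
| Objective 6 | adverse events, no limit | yes |
| Safety | adverse events, no limit, plus falls | not stated |
| Data analysis, objective 6 | adverse events pertaining to the study, no limit | yes |
| Adverse event; Related AE | definitions only, any severity | not applicable |
| Falls | any fall, injury not required | diary for all participants |
| Recording and reporting | serious only; capture, form and causality step for SAEs | not stated |

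The four promises and the reporting rule cannot all be followed.

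**Step 2. Find what falls in the gap.** Take all treatment-related events. Remove the serious ones, which go on the SAE form, and falls of any severity, which go in the diary. Non-serious related events other than falls remain. Pain, strain and dizziness from exercise are my examples; the article does not list them.

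**Step 3. Gauge the size.** The article states no event figure to reproduce and no expected rate, so the rates are assumptions, shown as a range. The 30 ARC participants come from the Qualitative analysis section and from 60 participants allocated 1:1. Randomisation is simple, so 30 is an expected rather than a fixed number. With a proportion p of participants having at least one such event, independently:

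- expected number affected = 30 × p
- chance of at least one = 1 − (1 − p)^30

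| Assumed p | Expected number of 30 | Chance of at least one |
|---|---|---|
| 5% | 1.5 | 1 − 0.95^30 = 0.785 (79%) |
| 10% | 3 | 1 − 0.90^30 = 0.958 (96%) |
| 20% | 6 | 1 − 0.80^30 = 0.999 (over 99%) |

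Under the rule as written, the number reported is zero in every row.

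**Step 4. See whether earlier evidence rules these rates out.** The Development of intervention section reports no intervention-related adverse events in the before and after study, where eight people received the intervention. The one-sided 95% upper limit for 0 of 8 is 1 − 0.05^(1/8) = 0.312, or 31%. All three assumed rates lie below it. This shows only that the earlier sample was small; it does not show that such events are common.

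**The case against.** The strongest counter-argument is that the word report refers to onward safety notification. The end of the recording section deals with notifying the chief investigator, the sponsor and the ethics committee, so the opening sentence could govern notification and leave the results tables alone. That is a fair reading of one sentence. It does not remove the conflict, because the section is also about recording, and it describes capture, form and causality step for SAEs only. The Causality section says who assigns causality in general, but gives no route by which a non-serious event reaches that person.

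A reader might infer that the likely harms of the exercise programmes go uncounted altogether. The article does not support that. A fall is the most obvious harm of gait and balance training, and falls of any severity are recorded in both arms. The recording section also adds a specific falls enquiry. A reader might likewise infer that objective 6 cannot be answered at all; SAEs and diary falls would answer part of it.

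Three other points stand in part:

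- The SAE definition includes events the investigator considers medically significant, so some important events without hospital admission can still be reported. Ordinary exercise-related pain or strain would not normally qualify.
- Exercises are supervised at first, and all community walking with the device is supervised. This may lower the event rate but does not supply a count.
- Answers to the outcome-visit question sit on the proforma and might be tabulated. Nothing in the article says so.

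The point does not depend on detail that a full protocol or analysis plan would add. It concerns a rule the article states, and an analysis plan cannot tabulate events that were not recorded.

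**Conclusion.** The contradiction is in the current text and needs correcting. Its reach is limited to non-serious treatment-related events other than falls. For those, the objective 6 count by arm has no stated source, and a low total would be partly a product of the rule. How many events would be missed cannot be known from the article; the 5% to 20% range and the independence of participants are assumptions, and the chance of losing at least one in the ARC arm runs from 79% to over 99% across that range.

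The severity is moderate. Adverse events are a secondary objective, they are not among the progression criteria, and no primary objective changes.

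**What to change.** Reconcile objective 6, Safety, Recording and reporting of adverse events, and the objective 6 analysis, and align the abstract with them.

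**Preferred.** Amend the recording section so that non-serious adverse events related to a study treatment or procedure are also recorded. Tabulate these, the SAEs and the diary-recorded falls by arm, each as number of events and number of participants with at least one event. Keep expedited reporting for SAEs only.

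Use the existing outcome-visit question as the common source, since it is put to both arms in the same way. Weekly provider contact is a weaker source: ARC participants have six supervised sessions, whereas weekly contact in the control arm may be face to face or by telephone, so ascertainment could differ by arm. The same caution applies to the weekly diary checks, which the Falls section describes as face to face. Causality should stay with the investigator, as the Causality section already provides, so that the blinded assessor need not learn the allocation.

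**Minimum.** Restate objective 6, the abstract, Safety and the objective 6 analysis as SAEs and falls only, so that the pilot does not claim wider safety evidence than it collects.

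**Cost.** The preferred option needs one log, some causality assessment and a short amendment. At submission of the article 16 of 60 participants had been recruited, so a change then could have applied in full to the remaining 44; earlier participants' events would be recoverable only as far as their proforma answers allow. The minimum option costs wording alone, but gives up information on tolerability.

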#### Data monitoring

A formal data monitoring committee or equivalent body will not be convened, as the study is of minimal risk and considered too small and of short duration to have official monitoring structures. However, there will be continuous ad hoc monitoring undertaken by study management. Safety data will be reviewed at project meetings. The treatment providers will closely monitor the well-being of individual participants. Stopping the study will be considered if the study management advises against continuing, for example study-related serious adverse events or falls. The chief investigator has the ultimate authority to stop or modify the study.

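### The quoted SAE question asks only about 'new' medical problems, but the protocol's own definition also counts worsening of existing conditions

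*Protocol article*

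**What the plan says.** The Safety section of the protocol article states: "The safety of the intervention will be evaluated by examining the occurrence of adverse events and falls". Under Recording and reporting of adverse events this is narrowed: "This study will only report adverse events which are considered to be serious".

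The definitions that decide what counts are these:

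- **Adverse event:** "Medical conditions/diseases present before starting study treatment are only considered adverse events if they worsen after starting study treatment". A worsening therefore qualifies.
- **Serious adverse event:** an untoward occurrence is serious if, among other criteria, it requires or prolongs hospitalisation. Nothing requires the underlying condition to be new.
- **Exclusions** (Recording and reporting of adverse events): only planned admissions and scheduled treatment of conditions already present.

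The same section describes how potential SAEs are found at the outcome assessments. The question it quotes from the proforma is "are there any new medical problems since the last study assessment". It then adds: "In addition, we will specifically enquire about falls in response to the participants falls diaries". If the team learns of an SAE at another time, "the SAE form will also be used to directly capture these events".

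Under Data monitoring, "The treatment providers will closely monitor the well-being of individual participants" and "Safety data will be reviewed at project meetings".

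**The concern.** The question used to find SAEs is narrower than the definition of the events it is meant to find. The definition has two branches, new occurrences and worsened existing conditions. The quoted question addresses only the first. A respondent who takes it at its word has no reason to mention the second.

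Because only serious events are reported, SAEs together with falls make up the whole safety output of the pilot. Objective 6 reports adverse events for each treatment as a number of events (Data analysis), and the project meetings review the same data. A narrow question can make that count too low. The wording could also be carried into the definitive trial that the pilot is meant to inform.

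**Working it through.** No arithmetic applies to the mismatch, so the check is to take types of event through the definitions and then through the planned enquiries.

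| Event during follow-up | Adverse event? | Serious? | Excluded? | Prompted by the quoted question? | Prompted by the falls enquiry? |
|---|---|---|---|---|---|
| New illness, unplanned admission | Yes | Yes | No | Yes | No |
| Fall leading to admission | Yes | Yes | No | Probably | Yes |
| Planned admission for a known condition | – | – | Yes | – | – |
| Known condition worsens, unplanned admission, no fall | Yes | Yes | No | Not if taken literally | No |

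The last row is the gap. The event meets the protocol's definitions, escapes both exclusions and is prompted by neither enquiry.

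The next step is to see what else could bring that event to the SAE form, by period.

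- **Weeks 1 to 6.** ARC participants have one supervised session a week (Procedures; Mode of delivery). Controls are contacted weekly, in person or by telephone (Mode of delivery, control treatment). Providers check the falls diaries weekly (Falls) and watch participants' well-being (Data monitoring). An admission would probably disrupt a contact and be noticed. None of these routes is a stated enquiry about worsening or admissions.
- **Weeks 6 to 10.** The treatment programme has ended. The one check that the text names for this interval is the outcome assessor's confirmation of falls (Falls). An admission without a fall has no other stated prompt until the 10-week question, which has the same wording.

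For size, let *w* be the share of all SAEs that are unplanned worsenings without a fall, *u* the share of those not volunteered in reply to the question, and *m* the share of the remainder that staff do not learn of otherwise. Then

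share of SAEs lost = *w* × *u* × *m*.

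The document gives none of the three. Since *u* and *m* each lie between 0 and 1, the loss lies between 0 and *w*, and *w* is itself unknown.

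**The case against.** Several points on the other side are sound.

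- **The article may not print everything.** It announces questions in the plural and prints one, and the proforma is not shown. A reader might infer that this is the only scripted question in the trial. The article supports only that it is the one question quoted. Even so, its wording is fixed in the text and is narrower than the definition.
- **Missing the event is not certain.** A reader might infer that a serious worsening would never be recorded. That goes too far. Someone recently in hospital may well mention it, whatever the exact wording. Assessors are to complete the form for any event that meets the SAE criteria, not only new conditions. In weeks 1 to 6 the weekly contact makes discovery likely. What remains is that these routes depend on chance awareness and are not systematic enquiries.
- **The class at risk is narrowed.** Study population excludes neurological, orthopaedic and cardiopulmonary conditions that affect gait or walking. Other chronic conditions remain eligible, so the class is smaller but not empty.
- **The decision weight is limited.** A reader might infer that an under-count would drive a wrong decision to continue. Data monitoring sets no rule based on an SAE count. Stopping is a management judgement, with serious events linked to the study, or falls, as examples. Adverse events are not among the Progression criteria, and Objective 6 is secondary and descriptive.

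A reader might also turn this into a point about delay: the weeks between assessments, the participants recruited meanwhile, or the 15-day notification to the ethics committee. Those concern the spacing of assessments and would be unchanged if the question were perfectly worded. The 15-day limit also covers only SAEs that are both related and unexpected.

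**Conclusion.** The mismatch stands. The quoted question covers new problems, while the protocol's definitions make an unplanned admission for a worsened known condition a reportable SAE. Such a participant, with no fall, can truthfully answer 'no'. Capture then rests on staff happening to find out, and the text offers least support for that between weeks 6 and 10.

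The size cannot be derived and may be zero. The effect is confined to the descriptive SAE count by arm under Objective 6 and to the safety data reviewed at project meetings.

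The conclusion rests on two assumptions: that the quoted wording is the wording used, and that no unprinted proforma item asks about worsening or admissions. If such an item exists, the point reduces to citing it in the text. This is a modest correction in a pilot described as minimal risk, but worth making because it brings the enquiry into line with the definition at almost no cost.

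**What to change.** Reword the proforma item used at the 6-week and 10-week assessments to match the definitions of adverse event and serious adverse event. For example: *Since your last study assessment, have you had any new medical problem, any worsening of an existing problem, or any hospital admission?* Keep the falls enquiry, and apply the existing exclusions for planned admissions and scheduled treatment when the answers are screened.

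The cost is one changed question, with no change to visits, treatment or analysis. The downside is a few more reported events to screen for seriousness. Trial status gives 16 of 60 participants recruited at submission, so 60 − 16 = 44 were still to be enrolled and could be asked the revised question throughout. The changeover date should be recorded so that the SAE counts can be read accordingly.

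Asking the same question at the weekly provider contacts is an optional extra. The mismatch does not require it.
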